**Fig. 4 Fig4:**
[figure not shown]
fNIRS test site diagram in task status

### Secondary results

It mainly includes assessment results in the cognitive domain (reaction time and accuracy, attention, memory, executive ability, fluency) and tests of cognitive behavioural ability levels.

#### Overall cognitive functioning was assessed using the following methods

The Montreal Cognitive Assessment Scale (MoCA), a test that includes 11 items on 8 cognitive domains including attention and concentration, executive function, memory, language, visual structure skills, abstract thinking, computation and orientation. With a total score of 30 and a normal score of ≥ 26, its high sensitivity, coverage of important cognitive domains and short test duration make it suitable for clinical use.Revised Addenbrooke’s Cognitive Examination (ACE-R (2012)), the ACE-R is a concise cognitive test that assesses the following 5 cognitive domains including attention/orientation, memory, verbal fluency, visuospatial and verbal cognitive abilities. The total score is 100, with the higher the score, the better the cognitive functioning.The stroop test measures the patient’s ability to categorise information from the environment and to respond selectively to information. It is used to assess the timing and accuracy of responses before and after pulmonary rehabilitation.The Simple Mental State Examination (MMSE) tests for cognitive impairment. The full scale is divided into five cognitive aspects: orientation, memory, attention and calculation, recall and language, and the results are rated on a total score of 30, with higher scores being better.

#### Specific cognitive domains are assessed by the following tests

The Paddle Elimination Test, a test in which five subtests are completed in 15 min, assesses the subject’s attentional direction and accuracy through the final score and failure rate.The Digit Breadth Test DST begins by reading aloud a string of random numbers at a rate of one digit per second and then asking the subject to repeat them out in either sequential or reverse order, with memory levels assessed based on accuracy of completion.The TMT Connect Test A-B, which consists of two sub-tests, A and B. The TMT-A tests “visuospatial ability” and “writing motor speed”, while the TMT-B tests “processing speed” and “cognitive flexibility”.The VFT verbal fluency test assesses the subject’s verbal ability, semantic memory, etc. The test requires the subject to say as many words of a certain type as possible within a specified time. It can be divided into semantic fluency, phonological fluency and motor fluency, with higher scores being better.The Berg Balance Scale (BBS) is examined in 14 items from easy to difficult. Each rated item is divided into five functional levels of 0, 1, 2, 3 and 4 to be scored. The minimum score is 0 and the maximum score is 56. The higher the score the better the balance.

#### Cognitive behavioural ability is measured by the following indicators

The physical exertion index (PCI) is the difference between the heart rate during the walking task and the heart rate at rest divided by the walking speed. Subjects’ cognitive abilities were assessed by using the PCI index to reflect changes in their cognitive abilities during the motor cognitive task.Timed-Stand-Walk (TUGT) is a measure of balance and agility that requires the subject to sit in a chair, time starts, the subject stands, and walks 3 m, then turns 180 degrees to return to the chair and records the time taken.The gait test analysis equipment was used to assess the patient’s level of cognitive behavioural ability in terms of changes in step frequency, step speed and walking time before and after the intervention in a 30-m rapid step speed task.

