For the measurement of the TSI, This study was designed to use a single-task walking test in two contexts. Also record the step frequency, step speed and walking time during the period. The first scenario was a single-task walk at a general pace (6 round trips on a 5-m trail analysis system for a total of 30 m). The general speed of the stride is based on the speed of walking at home. The second scenario is a fast walking single-task walk (6 round trips on a 5-m trail analysis system for a total of 30 m)[37, 38]. A fast walk is a guideline that mimics the speed of a fast walk through a junction. The status of altered cognitive function under the different intervention modalities was assessed by comparing oxygen saturation in the prefrontal cortex before and after the intervention, and by combining indicators such as step frequency, step speed and walking time during the period [39, 40]. In order to minimise experimenter-related methodological bias, the same assessor administered the same instructions to each subject. Each subject completed the task twice, once for familiarisation and once for assessment. Figure 4 shows the fNIRS instrument (portable NirSmart II-3000B Huitron Medical Devices Ltd.) that will be used in this study. It is possible to perform the relevant motor tasks in wireless transmission mode and record the cortical changes in oxyhaemoglobin during the performance of the task in continuous wave form. The light sources are fixed to the head cap at a distance of 30 mm, with a full channel sampling frequency of 11 Hz and wavelengths of 760 nm and 850 nm, respectively, with the detection area being the centre of each light detection point, and with specific brain area cues on the device to ensure accuracy of brain area monitoring.

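### Six physical measures are classed as cognitive outcomes, so a change in heart-rate cost, balance or gait could be read as a cognitive benefit

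*Protocol article*

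**What the plan says.** The secondary outcomes are set out in three blocks, which Table 1 repeats: overall cognitive function, specific cognitive functions, and cognitive behavioural assessment.

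- **PCI.** In the section on cognitive behavioural ability, PCI "is the difference between the heart rate during the walking task and the heart rate at rest divided by the walking speed". The next sentence says that subjects' "cognitive abilities were assessed by using the PCI index to reflect changes in their cognitive abilities during the motor cognitive task".
- **TUGT.** The same section lists it as an indicator of cognitive behavioural ability, but says that it "is a measure of balance and agility".
- **Gait.** The 30-m fast walk is taken as a gauge of "level of cognitive behavioural ability in terms of changes in step frequency, step speed and walking time before and after the intervention".
- **Berg Balance Scale.** It appears under the heading "Specific cognitive domains are assessed by the following tests": "The Berg Balance Scale (BBS) is examined in 14 items from easy to difficult". The only interpretation given is that a higher score means better balance.
- **The walking task.** The section on TSI, the main outcome, says: "This study was designed to use a single-task walking test in two contexts", one at usual pace and one fast.

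The control group has no systematic exercise rehabilitation and only routine medication. HG and BDJ each have three 40-minute sessions a week for 12 weeks.

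**The concern.** The trial asks whether head-down strong abdominal breathing improves cognitive function. An outcome can support that conclusion only if a change in it can be attributed to cognition. For these six measures, the article's own descriptions refer to something else.

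The labels also carry weight beyond the outcome lists. The abstract and the Introduction name the cognitive behavioural ability test as one of the means of assessing cognitive function. The TSI section assesses altered cognitive function by comparing prefrontal oxygenation together with cadence, speed and walking time, so gait enters the reading of the main outcome. The Discussion offers the cognitive behavioural tests, beside the scales, as support because fNIRS is prone to artefact.

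The comparison most exposed is an exercise arm against the control group. If training improves gait, balance or the heart-rate response to walking, the arms will differ on these measures whether or not cognition has changed. Nothing in the Statistical analysis section separates the two explanations.

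**Working it through.** The point concerns what is being measured, and the plan states no figure to reproduce. The check has three parts.

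**1. Definition against label**

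| Measure | Article's own description | Where it is filed |
|---|---|---|
| PCI | heart-rate rise on walking / speed | cognitive behavioural ability |
| TUGT | balance and agility | cognitive behavioural ability |
| 30-m pace, walking time, cadence | gait in a fast walk | cognitive behavioural ability |
| Berg Balance Scale | balance | specific cognitive domains |

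The PCI sentence calls the walk a motor cognitive task. The TSI section specifies single-task walking, and the Discussion says that the fNIRS analysis considers only the single-task condition. The article describes no walk with an added cognitive task. Elsewhere it keeps the two domains apart: Design and Randomisation and blinding speak of cognitive and physical tests, and the Discussion names cognitive function and motor ability as separate targets.

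**2. Row count in Table 1**

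- Overall cognitive function: MoCA, Stroop, ACE-R, MMSE = 4, none physical.
- Specific cognitive functions: TMT-A, TMT-B, DST, VFT, BBS, elimination test = 6, of which 1 is physical (BBS).
- Cognitive behavioural assessment: PCI, TUGT, pace, walking time, cadence = 5, all physical.

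Total: 4 + 6 + 5 = 15 rows, of which 0 + 1 + 5 = 6 are physical.

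**3. How PCI behaves**

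PCI = (walking heart rate − resting heart rate) / walking speed. The article gives no expected values, so every input here is assumed (heart rate in beats/min, speed in m/min).

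- Assumed start of 100 and 75 at 60: 25/60 = 0.417.
- Heart rates of 95 and 72, same speed: 23/60 = 0.383, and 0.383/0.417 − 1 = −8%.
- Heart rates of 95 and 72 at 66: 23/66 = 0.348, a change of −16%.
- A different assumed start, with a rise of 30 at 60: 30/60 = 0.50. With the rise 10% lower and speed 10% higher: 27/66 = 0.409, a change of −18%.

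No cognitive quantity enters any of these lines. Under the sentence on PCI, each fall would be taken to reflect a change in cognitive ability.

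**The case against.** **A reader might infer that a fitness gain will necessarily be reported as a cognitive benefit.** The article does not support that. It defines no composite, success rule or count across these measures. TSI is the main outcome, Secondary results names the cognitive domain and the cognitive behavioural tests separately, and each cognitive test has its own row. A reader of the results could see PCI move while MoCA does not. The risk is of misreading, and it should be stated as such.

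**A reader might also infer that walking carries no cognitive load, or that none of these measures has any cognitive content.** That goes beyond the text. Single-task means that no second task is added. The article does not say that walking makes no prefrontal demand, and it cites sources, not available here, for reading gait with TSI. Gait as an indirect marker is arguable. This defence is weakest for PCI, whose definition contains only heart rate and speed.

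**It is not shown that all six measures respond to both exercise programmes.** HG is mainly paced breathing on an inversion device, and no passage says that this improves gait or balance. The Introduction credits Eight Duan Jin with better exercise capacity, so the expectation is better grounded for BDJ. The argument also applies mainly against the control group and less to HG versus BDJ, where both arms are active.

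**The Berg entry may be a misplaced list item.** The Discussion names attention, memory, executive ability and fluency as the specific domains, without balance. That softens the point for BBS but leaves the explicit PCI and gait sentences untouched.

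**Pace and walking time might seem to be one measurement counted twice.** The article does not say how the gait system derives speed, so this is not established and no variable need be dropped.

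The Discussion also notes that fitness is positively associated with cognition in COPD. An association does not make heart-rate cost a measure of cognition; treating it as one assumes part of what the trial sets out to test.

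**Conclusion.** The point holds as a misclassification of secondary outcomes that also touches the interpretation of the main one. Six of the 15 rows under the cognitive headings, including every row of the cognitive behavioural block, are physical by the article's own definitions. PCI is the clearest case, because its formula and its stated use contradict each other in adjoining sentences. A difference in physical function, above all between HG or BDJ and the control group, could be read as a cognitive effect.

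The changes of about −8% to −18% in PCI show only how the formula behaves under assumed inputs. They are not an estimate of expected bias. The conclusion does not depend on them, or on the premise that walking is free of cognitive demand. It rests on the definitions, on the absence of an added cognitive task, and on the places where these measures are used as evidence on cognition. The recognised cognitive tests are unaffected.

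**What to change.** 1. Move BBS, PCI, TUGT, 30-m pace, walking time and cadence into a separate group of physical-function secondary outcomes, both in the two outcome sections and in Table 1.
2. Delete the statement that PCI reflects cognitive ability.
3. Amend the TSI section and the Discussion so that gait and the other physical tests are reported beside TSI and the scales as physical context, not as evidence of cognitive change. Without this step gait still enters the reading of the main outcome. Bring the matching phrases in the abstract and Introduction into line.
4. State that cognitive conclusions from the secondary outcomes rest on MoCA, ACE-R, MMSE, Stroop, TMT, DST, VFT and the elimination test.

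No data collection changes. The costs are fewer outcomes that can be cited for a cognitive effect, and a protocol amendment: the article requires a formal ethics application for any modification and, once approved, an update of the registry entry.

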### Safety

During the trial, safety officers will be available to monitor and assist those participating in the trial in real time. Any adverse events will be promptly recorded and reported to the principal investigator who will then decide whether they are related to the trial. When serious adverse events occur, clinicians at the People’s Liberation Army Naval Anqing Hospital will be notified so that they can provide timely treatment. For subjects who withdraw midway through the trial, the investigator must record the reason for withdrawal on the case report form, while maintaining contact with the subject, completing an assessment if possible, and completing an end-of-trial form.

### Experimental environment and data management

The experimental process will rely on community outpatient clinics to provide pulmonary rehabilitation interventions close to the patients, while the monitoring and collection of relevant data will be carried out at the People’s Liberation Army Navy Anqing Hospital. All medical records and assessment data collected from participants will be securely stored on an encrypted mobile hard drive. Only authorised research assistants will have access to the trial data. Blood samples will be stored and processed at the People’s Liberation Army Navy Anqing Hospital laboratory as required.

### Oversight and monitoring

#### Composition of the data monitoring committee, its role and reporting structure

The trial is low risk as the intervention is primarily delivered through exercise rehabilitation therapy accompanied by safety aids. The analyses of the primary outcome indicators will be relatively simple comparisons. An independent Data Monitoring Committee (DMC) was therefore not established.

#### Frequency and plans for auditing trial conduct

Formal trial auditing will not be carried out. This is because it is a low-risk intervention and the establishment of a DMC has not been considered.

#### Plans for communicating important protocol amendments to relevant parties (e.g. trial participants, ethical committees)

Any modification to the protocol, including changes in objectives, design, patient population, sample size and study procedures, required a formal application to the Ethics Committee of Anqing Normal University. If these modifications are approved, they will also be updated in a timely manner on the China Clinical Trials Registry (www.chictr.org.cn). At the same time, we will communicate it to the sponsors, and the investigators.

#### Adherence and adverse events

Adherence

Professionals such as exercise rehabilitators, respiratory physicians, nurses, and counsellors will be available to guide patients during the experiment. All patients will be followed up by telephone once a week to ask questions about their feelings, opinions or suggestions about participating in the experiment and to answer them. Also record the subject’s compliance with the trial protocol, including reasons why subjects did not meet the inclusion criteria (e.g. too young, wrong diagnosis); subjects did not complete all of the assigned intervention, or received another intervention, or did not even comply with the experimental intervention at all. The number of subjects who were unable to complete the trial and the reasons for this were recorded during the trial.

(2)Adverse events

The experiment is a low-risk intervention with no serious adverse effects or harm. Any adverse events during the trial, including dizziness, headache, and nausea, will be managed immediately by the healthcare professionals in the on-site research team.

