## Abstract

**Background:**

Patients with chronic obstructive pulmonary disease (COPD) often suffer from a combination of mild cognitive impairment (MCI) and a significant reduction in their quality of life. In the exercise programme of pulmonary rehabilitation (PR), pulmonary rehabilitation intervention is often carried out by enhancing respiratory function. Strong abdominal breathing is a kind of breathing method, through which the diaphragm can be exercised, thereby enhancing the deflection distance of the diaphragm during breathing and improving respiratory function. The inversion trainer can meet the different angles of head-down training and also has the characteristics of low cost, easy to operate, and use a wide range of scenarios. According to currently available data, strong abdominal breathing in combination with head-down position has not yet been used in pulmonary rehabilitation in this type of rehabilitation programme. It is valuable to use this device to study PR of cognitive function in patients with COPD.

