### Provisions for post-trial care

The experiment will be followed by a 6-month period with monthly telephone callbacks. At the same time, the trial was a low-risk intervention with no anticipated harm or compensation for participation.

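### Serious harm is ruled out before any data, and adverse events are observed far more closely in the exercise arms than in control

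*Protocol article*

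**What the plan says.** All references are to the protocol article.

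- **Adherence and adverse events** says: "The experiment is a low-risk intervention with no serious adverse effects or harm". It names dizziness, headache and nausea as possible events and has the on-site research team manage them.
- **Provisions for post-trial care** is milder: "the trial was a low-risk intervention with no anticipated harm or compensation for participation".
- **Abstract, Background** says that "strong abdominal breathing in combination with head-down position has not yet been used in pulmonary rehabilitation".
- **Safety** covers adverse events without limiting them to an arm: "Any adverse events will be promptly recorded and reported to the principal investigator who will then decide whether they are related to the trial". It also foresees serious events, in a sentence that begins "When serious adverse events occur, clinicians".
- **Adherence and adverse events** describes the one regular contact shared by all arms: "All patients will be followed up by telephone once a week to ask questions about their feelings, opinions or suggestions about participating in the experiment".
- **Intervention** gives HG and BDJ three sessions a week for 12 weeks. CG has routine medication and no exercise programme.

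**The concern.** There are two linked problems.

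First, a result is written as a premise. Whether the intervention causes serious harm in COPD patients with mild cognitive impairment is something the trial can inform, yet the protocol answers it in advance and cites no safety data with the sentence. The Discussion says that the angle and breathing rate were adapted from work in students and the elderly and will be assessed before the formal experiment. A reader of the final report could take a trial without serious events as confirmation, which an arm of this size cannot give.

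Second, the opportunity to notice an event differs by arm. Transient symptoms such as dizziness are readily seen by staff at a session. A CG patient has no sessions, and the stated content of the weekly call does not include a question on adverse events. If event counts are later shown by arm, an excess in HG or BDJ over CG could reflect closer observation, a true effect, or both. The same gap affects symptoms that HG patients have between sessions.

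**Working it through.** The protocol gives no safety figure to reproduce. The check has three parts.

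**1. The statements side by side.** Adherence and adverse events says there are no serious adverse effects. Safety says what happens when one occurs. Expecting low risk and planning for serious events are compatible; stating that there are none and planning for them are not. The milder wording in Provisions for post-trial care suggests that an expectation was meant.

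**2. Scheduled contacts per patient over 12 weeks.** Inputs: three sessions a week for 12 weeks in HG and BDJ (Intervention); no sessions in CG (Control group); one call a week for all patients (Adherence and adverse events), assumed to run through all 12 weeks.

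| Arm | Sessions | Calls | Total |
|---|---|---|---|
| HG | 3 × 12 = 36 | 12 | 48 |
| BDJ | 3 × 12 = 36 | 12 | 48 |
| CG | 0 | 12 | 12 |

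The ratio is 48/12 = 4 to 1 for either exercise arm against CG, and 1 to 1 for HG against BDJ. The three measurement periods (Design) are the same in all arms. Counting each as one contact gives 51 against 15, or 3.4 to 1.

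**3. What zero serious events in HG would show.** Inputs: 81 patients at 1:1:1, so 81/3 = 27 per arm; the calculated size of 69 gives 69/3 = 23 per arm (Sample size). With zero events in n patients, the exact one-sided 95% upper limit is 1 − 0.05^(1/n).

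- n = 27: 1 − 0.05^(1/27) = 0.105, or 10.5%.
- n = 23: 1 − 0.05^(1/23) = 0.122, or 12.2%.

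The first is the fairer figure, since serious events are normally counted in everyone exposed.

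The chance of seeing no event in 27 patients is (1 − p)^27. The protocol gives no rate, so p is assumed:

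| Assumed true rate | Chance of no event | Chance of at least one |
|---|---|---|
| 1% | 76% | 24% |
| 2% | 58% | 42% |
| 5% | 25% | 75% |

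At an assumed rate of 2%, a clean result is more likely than not.

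**The case against.** The case on the other side has real force.

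- **A reader might infer that the trial can neither support nor refute its safety statement.** The documents do not bear this out. Safety has any adverse event recorded and reported, so a related serious event in HG would refute the sentence. HG and BDJ also share one observation schedule, although the BDJ section as printed describes its 30-minute block as head-down breathing. If that is literal, CG is the only unexposed comparator; the passages must be reconciled.
- **A reader might infer that CG has no event capture.** It does. CG receives the same weekly call and the same assessments, and a question about feelings may bring out a symptom. That most CG events would be missed cannot be shown from the documents.
- **A reader might infer that the absence of a data monitoring committee, audit and compensation rests on this sentence.** The oversight sections cite low risk, along with safety aids and simple primary comparisons (for the committee) and the absence of a committee (for audit). They do not cite the absence of serious effects. The remark on compensation may simply mean no payment for taking part.
- **The article condenses a fuller protocol.** A call script or event form may exist there, and its absence here is not an error. This stands. The point is limited to what the article states about the call.
- **No between-arm safety comparison is planned.** This also stands, and it lowers the stakes. Imbalance matters only if counts are shown by arm.
- **The 10.5% limit is a property of any arm of 27 with no events, and the fix does not change it.** This is correct. The figure shows why the advance statement cannot be confirmed; it does not measure the imbalance in observation.

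The unsupported assertion, its conflict with Safety and the unequal observation remain.

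**Conclusion.** The point holds in a limited form. One sentence states as fact something not yet known for this population, conflicts with the provision for serious adverse events, and could not be established by this trial: no events in 27 HG patients is compatible with a rate up to 10.5%. Recording covers all arms, but scheduled contact runs at about 4 to 1 for each exercise arm against CG, and no adverse-event question is described for the contact that all arms share. Counts for HG or BDJ against CG would therefore not be comparable; HG against BDJ is balanced in schedule.

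This assumes 27 patients per arm, calls in each of the 12 weeks, and a call that asks no more than the article describes. If the full protocol already has an identical event question in the call, the second half of the point falls away and only the wording remains. Severity is minor to moderate: no planned efficacy analysis is affected.

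**What to change.** 1. Reword the sentence under Adherence and adverse events as an expectation, for example: the intervention is expected to be low risk in this population, and any serious adverse event will be recorded and handled as set out under Safety. Bring the two sections into agreement.
2. Add one short question, worded identically for HG, BDJ and CG, to the existing weekly call: dizziness, headache, nausea or any other event since the last call.
3. Tabulate call-elicited events by arm, as the comparable set. List events observed at sessions separately. If no serious event occurs in HG, report that with its exact upper confidence limit and do not present it as confirmation of safety.

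The cost is about a minute per call. With 81 patients and 12 calls each, 81 × 12 = 972 minutes, or roughly 16 hours of staff time over the trial, plus one table. More minor events will be recorded in every arm. No change to treatment or clinical management is involved.
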